## Abstract

**Introduction:**

Emergency department (ED) overcrowding is a global problem and a threat to the quality and safety of emergency care. Providing timely and safe emergency care therein is challenging. To address this in New South Wales (NSW), Australia, the Emergency nurse Protocol Initiating Care—Sydney Triage to Admission Risk Tool (EPIC-START) was developed. EPIC-START is a model of care incorporating EPIC protocols, the START patient admission prediction tool, and a clinical deterioration tool to support ED flow, timely care, and patient safety. The aim of this study is to evaluate the impact of EPIC-START implementation across 30 EDs on patient, implementation, and health service outcomes.

**Methods and analysis:**

This study protocol adopts an *effectiveness-implementation hybrid design* (Med Care 50: 217-226, 2012) and uses a stepped–wedge cluster randomised control trial of EPIC-START, including uptake and sustainability, within 30 EDs across four NSW local health districts spanning rural, regional, and metropolitan settings. Each cluster will be randomised independently of the research team to 1 of 4 dates until all EDs have been exposed to the intervention. Quantitative and qualitative evaluations will be conducted on data from medical records and routinely collected data, and patient, nursing, and medical staff pre- and post-surveys.

**Ethics and dissemination:**

Ethical approval for the research was received from the Sydney Local Health District Research Ethics Committee (Reference Number 2022/ETH01940) on 14 December 2022.

**Trial registration:**

Australian and New Zealand Clinical trial, ACTRN12622001480774p. Registered on 27 October 2022.

**Supplementary Information:**

The online version contains supplementary material available at 10.1186/s43058-023-00452-0.

Contributions to the literature
Implementation of interventions in emergency department settings is notoriously difficult due to workload unpredictability, high turnover, and undifferentiated nature of emergency department patients.Strategies to achieve successful clinician behaviour change and intervention implementation in this complex health care delivery setting are poorly understood.This large-scale implementation study will implement and evaluate an emergency model of care in rural, remote, and metropolitan emergency departments in NSW, Australia.The acceptability, adoption, appropriateness, costs, feasibility, fidelity, penetration, and sustainability will be tested and refined to inform future strategies for sustained implementation targeting clinician behaviour change in the emergency care context.

## Background

Emergency department (ED) overcrowding is a global problem associated with increasing demand for emergency care services and access block for patients requiring hospital admission [1, 2]. Patients seeking emergency care are routinely confronted by overcrowded waiting rooms and ambulance ramping where the demand for emergency care of clinicians systematically exceeds the supply. An ageing population, increase in chronic condition morbidity, and lack of access to primary care services further exacerbate increased demand for emergency care and ED overcrowding [3, 4].

ED overcrowding leads to treatment delays, reduced adherence to best practice guidelines, increased risk of error, and clinician burnout [3, 4]. Implications for patients are prolonged wait times leading to reduced quality of care and patient dissatisfaction with care. Furthermore, ED overcrowding can exacerbate existing health inequities, with vulnerable populations disproportionately disadvantaged due to increased wait times and reduced access to care.

Emergency clinicians treat patients of all ages, with varying degrees of clinical urgency and severity. Most patients attending the ED have undiagnosed, undifferentiated, and often painful conditions [5]. Delays in the comprehensive assessment, treatment, and escalation of care can be fatal. In Australia, only 63% of patients requiring ‘urgent care’ (i.e. triage category 3) were seen by medical officers within the required 30 min of ED arrival (2020–2021) [2, 6], with emergency nurses solely responsible for the care of these patients during this time. System interventions that aim to address patient flow are important in reducing overcrowding; however, strategies to address the impacts of ED overcrowding must be multi-factorial to ensure patients have access to timely and quality care.

The Emergency nurse Protocol Initiating Care—Sydney Triage to Admission Risk Tool (EPIC-START) is a model of care to optimise ED flow for quality and safety in emergency care (Fig. 1). EPIC-START is founded on systematic reviews of the literature [7, 8], research outcomes [9–11], and deep understanding of the real-world experience of clinical practice, education, and research in emergency care.

**Fig. 1 Fig1:**
[figure not shown]
Patient flow with and without EPIC-START

The *aim of this study* is to evaluate the EPIC-START system implications across 30 sites in NSW, specifically (i) to evaluate the implementation outcomes: acceptability, adoption, appropriateness, costs, feasibility, fidelity, penetration, and sustainability; (ii) to evaluate the patient and health service outcomes. We hypothesise the use of the EPIC-START model of care in the ED will be associated with (i) reduced patient length of stay, (ii) improved patient time to treatment safety outcomes and clinician experience, and (iii) time to treatment compared to standard care.

## Methods

An effectiveness-implementation hybrid design [12] incorporating a stepped–wedge cluster randomised control trial (SWRCT), including uptake and sustainability, will be conducted to evaluate the EPIC-START model of care. The study is a partnership between academic researchers, clinicians at the sites, and policymakers within the NSW state government and non-government organisations. Reporting has been formatted with Consolidated Standards of Reporting Trials (CONSORT) extension for the SWRCT and SPIRIT (Standard Protocol Items: Recommendations for Interventional Trials) statement [13] (Supplementary materials 1 and 2).

### The intervention

EPIC-START combines validated data analytic tools with early nurse-initiated care protocols. The EPIC-START model of care incorporates three components: (i) EPIC, (ii) START, and (iii) a deterioration tool. An example of the clinical application of EPIC-START is presented in Fig. 2.

**Fig. 2 Fig2:**
[figure not shown]
Example of the EPIC-START model of care in action

Emergency nurse Protocols Initiating Care (EPIC) is a clinical framework to support the early delivery of standardised evidence-based treatment by emergency nurses for the most common ED presentations. There are 73 EPIC protocols—41 adult and 32 paediatric—which were developed in 2021–2022 by the NSW Agency for Clinical Innovation (ACI) with clinician and policy stakeholders (see NSW Health website). All EPIC protocols are structured on the validated HIRAID™ emergency nursing framework (History, Identify Red flags, Assessment, Interventions, Diagnostics, communication and reassessment) [10]. The EPIC component of EPIC-START is planned for staged state-wide implementation in 2023.

The second component is the Sydney Triage to Admission Risk Tool (START), which is a validated decision support/risk assessment tool at the point of triage [14]. This tool combines the presenting health concern with various other data elements available at the point of triage to estimate the risk of hospital admission or discharge to support senior clinical decisions about streaming and disposition from ED. The START component has been piloted and evaluated in Sydney, NSW [9, 14].

The third element is a clinical deterioration tool that uses an alert system to support earlier detection of, and senior medical response to, patients at risk of clinical deterioration. The clinical deterioration alert system is based on the Modified Early Warning Score (MEWS) [15]. This validated tool estimates the risk of clinical deterioration resulting in death or intensive care unit admission based on vital sign observations routinely recorded by clinicians in the electronic medical record (eMR) observation charts with a reported AUROC of 0.83 (95% CI, 0.83–0.84) [16]. MEWS is one of many early warning scores available that was chosen because of its high sensitivity to the general ED population, and because it uses data that is routinely collected in Australian EDs. Other tools have items such as hypercapnic respiratory failure, which are not routinely collected [17].

### Trial design

The *effectiveness-implementation hybrid design* [12] comprises a closed cohort stepped–wedge cluster randomised controlled trial supported with implementation frameworks to test the implementation strategy and the outcomes of the intervention. A stepped–wedge cluster randomised controlled trial design is considered appropriate for implementation evaluations of health service interventions as it simplifies data collection procedures, supports logistical processes better, aligns with ethical principles, accommodates temporal issues, and optimises financial constraints. The stepped–wedge cluster randomised controlled trial addresses the ethical dilemmas of randomised trial design where essential investigations and/or best-practice treatments may be withheld from control participants [12].

The closed cohort stepped–wedge, cluster randomised controlled trial design involves a sequential rollover of the intervention at four local health district clusters after baseline. This study will be conducted in four local health districts in NSW, Australia. Each cluster will begin in the control condition (baseline data collection) and will sequentially receive the intervention at 6-week intervals.

### Randomisation

Each cluster will be randomised independently by the research team to 1 of 4 dates until all EDs have been exposed. The clusters will be randomised using a computer random number generator to the dates that will implement. Once the initial randomisation of clusters has occurred, all investigators will know the order in which implementation will occur. However, study clusters will be blinded for the analysis.

### Setting

This study will include all patients presenting to one of 30 emergency sites across four local health districts in NSW, Australia (24 EDs/6 multi-purpose services). Multipurpose services provide flexible services to regional and remote communities with integrated health and aged care services [18]. The sites vary in size and are in rural, regional, and urban contexts. The number of sites varies with the geography of each cluster, representing real-world conditions. The sites combined employ approximately 1300 emergency nurses and see over 650, 000 presentations per year (Table 1).

**Table 1 Tab1:** Local health district (LHD) clusters: ED patient and nurse numbers; patient treatment times; and experience

Cluster	ED patients per year (2020–2021)	Patients (%) whose treatment started within recommended timeframes by triage category			ED nurses	Patient rating (%) ‘very good’ care (2019–2020)
		Cat 2 (10 min), target 80%	Cat 3 (30 min), target 70%	Cat 4 (60 min), target 70%		
Northern NSW (8 EDs, 3 MPS)	198,380	69	70	76	430	70
Sydney LHD (3 EDs)	163,839	48	67	81	402	65
Western Sydney LHD (4 EDs)	197,279	28	52	69	280	48
Southern NSW (8 EDs, 4 MPS)	107,073	66	71	79	180	69
Total (30 EDs/MPS)	666,571	53	65	76	1292	63

*MPS* Multipurpose service, *ED* Emergency department

### Participants

There will be four participant groups in this trial:
*ED patients (medical record audits)*: Routinely collected patient-level medical record data including patient presentation information and costing data will be analysed. All patients (adult and paediatric) presenting to the ED during the collection period for each cluster will be included. Patients requiring immediate resuscitation or direct transfers/admissions from other sites will be excluded from the data.
*ED nursing staff (surveys)*: All registered nurses permanently employed in the EDs/multi-purpose site across each local health district will be invited to participate in pre- and post-implementation surveys.
*ED medical staff (surveys)*: All medical staff employed regularly in the EDs/multi-purpose site across each local health district will be invited to participate in pre- and post-implementation surveys.
*ED patients /carers (surveys)*: Any patient with an ED visit during the survey data collection time will be included. A carer may also complete the survey for paediatric patients under 18 years or patients with cognitive disabilities. Patients with a triage category of one (immediate) or presenting for end-of-life care will be excluded, as well as patients or their carers with cognitive impairment, such as intoxication or dementia.

### Study plan

The study will be conducted over four stages (Fig. 3). A logic model depicting the implementation plan has been developed and will be updated after each stage [19].

**Fig. 3 Fig3:**
[figure not shown]
The four stages of the EPIC-START research project

#### Stage 1: Identify the barriers and facilitators to EPIC-START implementation and use

Behaviour mapping will be undertaken to obtain baseline data prior to the design of a context-specific intervention strategy for EPIC-START. Behaviour mapping will help (1) determine who needs to do what differently, (2) understand the barriers and facilitators for implementation (using the behaviour change wheel [20]), (3) identify the components (behaviours, mode(s) of delivery) that could be overcome to modify the barriers and enhance the facilitators, and (4) identify which interventions can be measured and understood [12]. The Theoretical Domains Framework [21] in conjunction with the Consolidated Framework for Implementation Research (CFIR) [22] will be used to understand the site and individual determinants, i.e. barriers and facilitators to implementation. The CFIR will be used to assess site contexts.

##### Data source

Nursing staff, medical staff, and patient/carer experience pre-implementation surveys will inform stage 1. All data will be managed on a secure platform (REDcap™—Research Electronic Data Capture—https://catalyst.harvard.edu/services/redcap/).

##### Outcomes

The outcomes of stage 1 will be the barriers and facilitators to EPIC-START implementation that are necessary to develop an effective and sustainable EPIC-START implementation strategy (stage 2) that maximises consistent and appropriate uptake. These data will guide the implementation strategy and adaptations that need to be made for implementation. It will also be used to compare sites during evaluation (stage 4) [23].

#### Stage 2: Develop site-specific EPIC-START implementation strategy

An implementation strategy for each cluster will be co-created with site end-users, nurse educators, and the hospital executive through an iterative process guided by the behavioural change wheel (BCW) [20]. The identified aspects of behaviour (including organisational barriers) will be mapped to intervention functions and behaviour change techniques. Intervention functions are ‘broad categories by means of which an intervention can change behaviour’ [20]. We used this approach successfully to test interventions in the ED previously (2021) [10, 24, 25]. The implementation toolkit will be refined for each cluster using mechanisms from the behaviour change techniques taxonomy and the APEASE criteria that consider affordability, practicality, effectiveness/cost-effectiveness, acceptability, side-effects/safety, and equity [20]. Readiness assessments and close consultation with stakeholders at sites and NSW Health will also inform this stage.

##### Sources

The results of the survey from stage 1 and implementation science frameworks (BCW, CFIR).

##### Outcomes

A behaviour change–informed implementation strategy for EPIC-START to be implemented and used in stage 3.

#### Stage 3: Implement EPIC-START

Implementation of the EPIC-START model of care will occur sequentially at the clusters to ensure geographically and clinically diverse ED settings using the strategies identified as effective in stage 2. These strategies will be applied consistently to ensure implementation fidelity*.*

Ongoing implementation support strategies will continue during the implementation stage: for example, the staff at each site will continue to receive support and coaching from the implementation team and updates on the implementation efforts. An implementation nurse will manage each cluster funded by the study. Following implementation, EPIC-START will become part of routine mandatory training to ensure sustainability.

##### Education and training of nursing staff

The education programme will be purposefully designed by educational experts, together with frontline emergency nurses, to frame many of the interventions emergency nurses already use, drawing on the best available evidence regarding patient assessment, risk factors for adverse outcomes, and educational pedagogy to develop deep learning of core concepts and high order thinking. The learning resources (pre-reading, participant workbook, e-learning module, and facilitated interactive workshop) use the educational principles of constructive alignment, backwards design, and scaffolded learning [26–30]. Training in HIRAID™ is a prerequisite to EPIC training in the study sites because effective emergency nursing assessment is essential to patient safety and choosing the correct EPIC protocol to initiate for the undifferentiated patient.

##### Environmental changes

Already brokered agreements with the local health districts will ensure the smooth implementation of EPIC-START. Scoping work around incorporating the START and the deterioration tool within eMR will also be undertaken across sites. In addition, hospital bed managers will be engaged in a brief 1-h education session at each site on the use of the START at triage and its implications for patient flow.

#### Stage 4: Evaluate the effectiveness of EPIC-START

The effectiveness of EPIC-START will be evaluated during stage 4 with the question: ‘Will implementing EPIC-START deliver timely and cost-effective care that improves patient health outcomes?’. Five hypotheses will be tested (Fig. 4): As a result of the implementation of EPIC-START:H1: Patient LOS in ED is 1 h shorter.H2: There is a 5% increase in care started in the national timeframe.H3: There is a 20% faster time to analgesia.H4: 5% more patients report ED experience as ‘very good’.H5: Overall acute treatment costs are reduced.

**Fig. 4 Fig4:**
[figure not shown]
Model of the study with outcomes and hypotheses

##### Sources

Site clinical governance/performance units, electronic medical records, ED performance data, hospital clinical costings, and Incident Information Management System and Performance Unit databases for each of the 30 sites: nursing staff survey, medical staff survey, and patient experience surveys. Implementation logs will be used by the implementation nurses to report on adaptation the implementation log developed using the Framework for Reporting Adaptations and Modifications-Expanded (FRAME) [31].

##### Populations

All participant groups will be used in the evaluation: ED patients, nursing staff, medical staff, and patient experience surveys.

##### Outcomes

Outcomes are summarised in Fig. 4. Outcomes of acceptability, adoption, appropriateness, feasibility, fidelity, implementation cost, penetration, and sustainability will be evaluated [32]. Fidelity is important to control for the differences in intervention delivery between sites and is critical for the internal and external validity of the trial. Implementation fidelity will be measured through a validated tool and informed by site audits and EPIC nurse trainer implementation logs. Descriptive statistics will be used to describe reach, fidelity, and exposure dose to (1) determine acceptability and end-user experience of EPIC-START (i.e. ED clinicians, hospital managers, and consumer representatives) and (2) gain insights on how EPIC-START could be improved and implemented across all Australian EDs.

### Sample size

Sample size calculations considered the estimated between-cluster variance, i.e. between local health district variance, and the design effect associated with the stepped-wedge design [33]. Calculations were based on previous studies and local health district information. Not many previous similar cluster randomised studies have reported the intraclass correlation coefficient (ICC). One similar study on ED LOS used an ICC of 0.18 [34] and another one in community outpatient services but examined waiting time after triage used an ICC of 0.01 [35]. To be conservative, an ICC of 0.05 has been applied in the calculation. Sample sizes relative to the hypotheses are below:
*H1: Patient LOS in ED is 1 h shorter*: The number of ED presentations required per data collection time point at each cluster is 1420 to detect a 1-h change in ED LOS for a two-sided test (80% power; α < 5%), assuming a standard deviation of 5.4 h [36].H2: There is a 5% increase in care started in the national timeframe: To detect at least a 20% increase for Triage Cat 2 and 3 patients, a total of 1920 patients will be required (120 per local health district per quarter).H3: There is a 20% faster time to analgesia: To detect at least a 5% reduction in time to analgesia, 960 patients will be required (60 per local health district per quarter). This is achievable for our 20% target.H4: 5% more patients report ED experience as ‘very good’: To detect at least a 5% increase in the rating as ‘very good’ in the intervention group, compared with the control group, 1920 patients will be required (120 per local health district per quarter).

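### H1's 1420 presentations per cluster and time point does not follow from its stated inputs (about 143), and calling an ICC of 0.05 conservative is unsupported

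*Protocol article*

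**What the plan says.** The Sample size section says that the calculation used the between-LHD variance and "the design effect associated with the stepped-wedge design". For H1 it states: "The number of ED presentations required per data collection time point at each cluster is 1420 to detect a 1-h change in ED LOS". The other H1 inputs are 80% power, a 5% two-sided significance level and an SD of 5.4 h.

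On the ICC it cites two sources. The first concerns the H1 outcome: "One similar study on ED LOS used an ICC of 0.18". The second is an outpatient study of waiting times, with a value of 0.01. The section settles on a figure between the two: "To be conservative, an ICC of 0.05 has been applied in the calculation".

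The layout is in the Trial design section: the design "involves a sequential rollover of the intervention at four local health district clusters after baseline", at 6-week intervals. The Statistical methods section adds fixed effects for intervention status and for time point, baseline included. No correlation between periods within a cluster, and no other inflation factor, is given.

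**The concern.** Every input that a standard stepped-wedge calculation needs is printed, apart from the exact number of measurement periods, which can be read from the design description. The H1 figure can therefore be checked, and it comes out about ten times too high for the unit in which it is stated.

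The ICC sentence has a separate problem. Of the two values cited, 0.18 belongs to the H1 outcome and 0.01 to a different outcome in a different setting. A value below the only one for ED length of stay needs a reason before it can be called conservative, and none is given.

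What is at stake is the meaning of the sample size statement. A reader cannot tell which difference the trial is sized to detect, or what limits its precision.

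**Working it through.** **Inputs.** Difference 1 h, SD 5.4 h (variance 29.16), two-sided 5%, 80% power, ICC 0.05: Sample size. Four clusters, one baseline, four steps: Trial design and Statistical methods. One measurement per period, hence five periods, is my reading.

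**1. Stepped-wedge design effect.**
- Unadjusted total: 4 x (1.96 + 0.8416)² x 29.16 = 915.5.
- Design effect with k = 4 steps, b = 1 baseline, one measurement per step and n per cluster-period: [1 + ρ(kn + bn − 1)] / [1 + ρ(kn/2 + bn − 1)] x 3(1 − ρ) / [2(k − 1/k)].
- At n = 142: [1 + 0.05 x 709] / [1 + 0.05 x 425] x 2.85/7.5 = (36.45/22.25) x 0.38 = 0.6225.
- Per LHD per time point: 915.5 x 0.6225 / 4 = 142.5, so 143. The stated 1420 is 9.97 times 142.5.

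**2. Check by the Hussey-Hughes variance.** With τ² = ρ x 29.16 and s = (1 − ρ) x 29.16/n, four clusters and five periods give

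Var = 4s(s + 5τ²) / (10s + 30τ²).

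- ICC 0.05: τ² = 1.458 and s = 27.702/n.
- n = 142: s = 0.1951, Var = 0.1278, SE = 0.3575 h. Power = Φ(1/0.3575 − 1.96) = 79.9%.
- n = 1420: s = 0.01951, Var = 0.01298, SE = 0.1139 h. Power = Φ(8.78 − 1.96), above 99.9%. Detectable difference at 80% power: 2.8016 x 0.1139 = 0.32 h.

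**3. Can another reading give 1420?**
- Other layouts with one measurement per step (three or four steps, none to two baseline periods) give about 129 to 239 at ICC 0.05. Dropping the baseline, for example, gives about 169.
- 90% power gives 191.6.
- A t reference distribution with only 2 degrees of freedom gives 97.8% power at 1420, still not 80%.
- The five-period layout has 10 control and 10 intervention cluster-periods. 142 x 10 = 1420, so the figure matches a total per condition.

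**4. Effect of the ICC under the same model.**

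| ICC | n per LHD per time point | Power at 1420 |
|---|---|---|
| 0.01 | 139.5 (140) | >99.9% |
| 0.05 | 142.5 (143) | >99.9% |
| 0.18 | 124.5 (125) | >99.9% |

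The requirement peaks near ICC 0.02 and then falls. No value in the cited range is conservative by a meaningful margin.

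**5. Sensitivity to an assumption outside the document.** Let the cluster effect have autocorrelation π between periods. Replace τ² by ρ x 29.16 x π and add ρ x 29.16 x (1 − π) to s. Mean volume is 666,571/4 x 6/52, about 19,000 per LHD per 6 weeks. At π = 0.90 (assumed) and ICC 0.05: s = 0.00146 + 0.1458 = 0.1473, τ² = 1.3122, SE = 0.311 h, detectable difference 0.87 h. Likewise 0.40 h at ICC 0.01 and 1.65 h at ICC 0.18.

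Power for 1 h at n = 1420:

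| ICC | π = 1.00 | 0.95 | 0.90 | 0.80 |
|---|---|---|---|---|
| 0.01 | >99.9% | >99.9% | >99.9% | 99.4% |
| 0.05 | >99.9% | 98% | 86% | 61% |
| 0.18 | >99.9% | 64% | 39% | 23% |

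**The case against.** The strongest reply is that the figure may rest on inputs that the article does not print. It refers to previous studies, to LHD information and to a cited method. An autocorrelation of about 0.88 at ICC 0.05 would make 1420 give 80% power. This is a fair reason not to insist on printing 143, which under drift would be too few. It does not vindicate 1420, because no such parameter is stated. The number of periods is also a reading, but the alternative layouts do not close the gap.

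The practical effect is small, and that stands too. All eligible presentations are to be included, and the smallest LHD (107,073 a year) sees about 107,073 x 6/52 = 12,400 in six weeks. Neither 143 nor 1420 determines how many patients are analysed.

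A reader might go further and infer that the wrong number and the low ICC together leave H1 short of 80% power. The document does not support that. A requirement stated ten times too high cannot cause a shortfall, and under the standard model an ICC of 0.18 needs fewer presentations than 0.05. The low power figures above arise only with an autocorrelation below 1, which the document never gives. Within the assumed range, power stays above 80% at ICC 0.01 throughout, and at ICC 0.05 when the autocorrelation is 0.90 or more.

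**Conclusion.** Two separate points hold. First, 1420 per LHD per time point does not follow from the stated inputs. They give about 143, a factor of ten, and 1420 would correspond to power above 99.9% or a detectable difference of about 0.32 h. This rests on the five-period reading, a normal approximation and a single random cluster effect. Whether the cause is a mislabelled per-condition total, a decimal slip or unstated inputs cannot be settled from the document. Second, the conservative label for ICC 0.05 is unsupported against the cited 0.18, and has little meaning in a model where the ICC barely moves the requirement.

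The tenfold error itself does not threaten power. With only four clusters, H1 would be sensitive to LHD means drifting over time, but the size of that effect is conditional on an assumption from outside the document. Confidence is high for the arithmetic only.

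**What to change.** - Correct 1420 or its unit, or state the inputs that yield it, including the number of periods and any between-period correlation. Do not simply substitute 143.
- Delete the words that present 0.05 as conservative, and give the reason for choosing it.
- Restate H1 as power or detectable difference at each LHD's actual volume, over ICC 0.01 to 0.18. The LHDs range from 107,073 to 198,380 presentations a year, so the mean of about 19,000 per six weeks is only illustrative. Mark any cluster autocorrelation explicitly as an assumption and show a range.

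The cost is a text change and a short recalculation. No patients are added. The stated power may become less favourable.

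### H2 hypothesises a 5% increase but its 1,920 patients are sized for a 20% increase, and H4 gives the same 1,920 for a 5% effect

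*Protocol article*

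**What the plan says.** The section on Stage 4 lists the hypotheses, among them "H2: There is a 5% increase in care started in the national timeframe". The Sample size section presents its numbers as belonging to those hypotheses. For H2 it repeats the 5% and, in the same sentence, plans for another effect: "There is a 5% increase in care started in the national timeframe: To detect at least a 20% increase for Triage Cat 2". Cat 3 is included as well, and the total is 1,920 patients, which it breaks down as 120 per local health district (LHD) per quarter. It does not say whether either percentage is absolute or relative, or from what baseline.

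For H4 the same section gives the same 1,920 and the same 120 per LHD per quarter, this time "To detect at least a 5% increase in the rating as ‘very good’ in the intervention group".

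For H3 the order of the two figures is reversed: "There is a 20% faster time to analgesia: To detect at least a 5% reduction in time to analgesia, 960 patients will be required". The section then adds: "This is achievable for our 20% target".

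**The concern.** For H2 the planning effect is four times the hypothesised effect. That is the unsafe direction, because the number needed rises roughly with the inverse square of the effect. A sample just adequate for 20% falls well short for 5%. A reader who takes 1,920 as the number that supports H2 is misled about the power for the hypothesis as written.

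The repeat of 1,920 under H4 is a second sign of trouble and needs no outside figure. H2 and H4 both concern proportions with baselines in the same region, yet one number is offered for a 20% effect and for a 5% effect.

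**Working it through.** **Inputs.** From the article: effects of 5% and 20%; 120 per LHD per quarter; four LHDs, one per start date (Trial design); ICC 0.05 (Sample size). Two-sided 5% and 80% power are stated for H1 only, and I assume them for the rest. Baselines come from the Total row of Table 1: Cat 2 53%, Cat 3 65%, rated very good 63%. The article does not name these as planning rates, so using them is also an assumption.

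**The plan's own totals.** 120 × 4 LHDs × 4 quarters = 1,920 and 60 × 4 × 4 = 960. Both multiplications are right. How 120 and 60 were derived cannot be reproduced uniquely, because baseline and scale (H2) and SD (H3) are not stated.

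**Without clustering.** Usual two-proportion formula, pooled variance under the null, 80% power:

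| Effect | Total from 53% | Total from 65% |
|---|---|---|
| +5 points | 3,100 | 2,754 |
| +5% relative | 11,092 | 6,608 |
| +20% relative | 678 | 378 |
| +20 points | 182 | 146 |

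Split 960/960, 1,920 patients have 60-65% power for +5 points and 21-33% for +5% relative.

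**Stepped wedge (Hussey-Hughes).** With I clusters, T periods and m patients per cell:

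Var = I·s²(s² + T·t²) / [(I·U − W)s² + (U² + I·T·U − T·W − I·V)t²]

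Here s² = (1 − ICC)·v/m, t² = ICC·v, and v = p(1 − p) at the mean of the two rates. U is the number of exposed cells; W and V are the sums of squared column and row totals of the exposure matrix. Four sequences give U = 10, W = 30, V = 30.

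- T = 5 (one baseline period, 2,400 records), v = 1: s² = 0.95/120 = 0.00792, t² = 0.05. Var = 4 × 0.00792 × 0.2579 / (10 × 0.00792 + 30 × 0.05) = 0.00517, so SE = 0.0719 SD.
- T = 4 (no all-control period, 1,920 records): the last coefficient is 20 instead of 30. Var = 0.00610, so SE = 0.0781 SD.

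Power = Φ(effect/SE − 1.96). For +5 points from 53%, SD = 0.497. At T = 4 the SE is 0.0388 and power is 25%; at T = 5 the SE is 0.0357 and power is 29%. All cases, as T = 4 / T = 5:

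| Effect | From 53% | From 65% |
|---|---|---|
| +5 points | 25% / 29% | 28% / 32% |
| +5% relative | 10% / 11% | 14% / 16% |
| +20% relative | 79% / 85% | 96% / 98% |
| +20 points | >99% | >99% |

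For 80% power at +5 points with T = 5, the cell size must be 489 (from 53%) or 434 (from 65%). Times 20 cells, that is 9,780 or 8,680 records.

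**H2 against H4.** From 63%, +5 points needs 2,836 patients without clustering, and +5% relative needs 7,236. The largest H2 requirement for a 20% effect is 678. The H4 requirement is therefore at least 2,836/678 = 4.2 times that of H2, and a shared method, ICC and power cannot give one number for both. In the stepped wedge, 120 per cell gives H4 about 27-31% power for +5 points.

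**H3.** At 60 per cell the SE is 0.109 SD (T = 4) or 0.101 SD (T = 5). The detectable difference at 80% power is 2.80 × SE = 0.30 or 0.28 SD. A 5% reduction is then detectable if the SD is at most 0.05/0.304 = 16% to 0.05/0.282 = 18% of the mean. A 20% reduction needs an SD of at most 66-71% of the mean.

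**The case against.** **The H2 analysis will use far more than 1,920 records.** This stands. The Participants section includes all eligible presentations, and Table 1 shows 666,571 a year before exclusions. Even the smallest district has 107,073/4 ≈ 26,800 a quarter in all triage categories, against the 489 per cell found above; the share in Cat 2 and 3 is not given. A reader might infer from the 25-32% that the H2 analysis itself is underpowered. The documents do not support that: 1,920 is a planning minimum.

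**H3 shows the same mismatch, so neither number supports its hypothesis.** A reader might infer this, but it does not follow. H3 is planned for a smaller effect than its target, which is conservative: at a given SD, 20% needs about one sixteenth of the patients that 5% needs. The article itself presents 5% as the minimum detectable effect and 20% as the target. Any claim that 960 is too few rests on an SD that the article does not give, and a condensed article may leave that to the full protocol.

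**The 5% and 20% were simply swapped between H2 and H3.** This is tempting. The closed-form stepped-wedge design effect for this layout is about 0.62, and 3,100 × 0.6206 ≈ 1,924, which suggests that 1,920 was meant for 5 points from 53%. But a 20% relative rise from 53% also has 79% power at 1,920 in the 4-period model, so the origin cannot be settled. Even on the first reading, the model above asks for about 8,700-9,800 records.

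**H2 and H4 measure different things in different populations.** True, and the comparison does not show which statement is wrong. It shows only that both cannot come from one common calculation.

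**Conclusion.** The point holds for H2. The hypothesis and the planning effect contradict each other, and 1,920 as justified does not support a 5% increase. That conclusion is the same on the absolute and relative scales, from 53% or 65%, and with or without clustering. Its exact size depends on the assumed baselines, on carrying the H1 error rates over to H2, and on 4 or 5 periods at 120 per cell. The shared 1,920 puts the H4 statement in question as well.

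The defect is in the published sample-size justification, not in the data to be analysed for H2. For H3 there is no failure to report; at most, the SD assumed in planning should be compared with the 16-18% of the mean that a detectable 5% reduction implies.

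**What to change.** - **H2:** make the planning effect equal to the 5% hypothesis, or change the hypothesis in Stage 4 if 20% was intended. State whether the effect is absolute or relative, the baseline, the power and the number of periods. Then restate the required number, or the power that the available records give.
- **H4:** recompute 1,920 by the same method and with the same ICC.
- **H3:** say plainly that 5% is the minimum detectable effect and 20% the target, and check the assumed SD against the limits above.

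For H2 the cost is a text correction and a recalculation; no further data collection is needed, because routine records are used. H4 relies on patient surveys, so if its check shows a shortfall, the plan would have to state the lower power or seek more responses.
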